### Sample size

The most significant variable in palliative care patients is assumed to be anxiety. In a review conducted by Bradt et al. [29], this variable presented a distribution with a standard deviation of 1.8, for a population similar to that considered in the study we propose, albeit with a wider range of results. Previous studies have reported that music therapy has a significant impact on this variable. In one case, an effect size of 7 was measured (effect size of 29% of the standard deviation). Another study, of cancer patients receiving treatment including ginseng [39], recorded a variation of 0.83 points on the Edmonton scale, with a standard deviation of 2.34 (35% of the standard deviation). Assuming a 2-point decrease in before-after anxiety to be clinically relevant, and a maximum standard deviation of 2.5 in our population, with an alpha error of 0.05 and a beta of 0.10, we calculate that two samples of 33 subjects will be necessary, to enable the option of a 1:1 ratio between the samples. For convenience, and to allow for losses to follow up, this sample size will be increased by 20%, to two samples of 40 persons. The Epidat 4.2 statistical program was used to perform these calculations.

Hanser et al. [40] recorded an increase in caregivers’ satisfaction following the incorporation of music therapy into the healthcare provided, with a standard deviation of 1.33 for relaxation, 1.87 for comfort, and 1.23 for happiness. Taking into account these findings and assuming an increase of one point in the dimension of caregiver happiness to be clinically relevant, we calculate that two samples of 34 caregivers will be necessary. For convenience, this sample size will be increased by 20%, to two samples of 41 persons, to allow for losses to follow up.

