If the patient is a member of the intervention group, in addition to the above, the researcher will ask them to make a list (at home) of 15 songs or musical items that put them in a good mood, and to send it (by mail or by phone) to the researcher so that the titles selected can be obtained and made ready for the beginning of the sessions, available either on the mp3 player or through the music app of the mobile phone. Participants in the control group will listen to health education advice, on the mp3 player or via Google Drive on their mobile phone.

The case management nurses at the six healthcare centres collaborating with this study will evaluate the study variables at three time points: 1 day before the participant receives the music delivery system from the researcher, 7 days after the intervention and 30 days after the intervention. These nurses will be blinded to the study group to which the participant is assigned.

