### Outcome assessment

The primary outcome measures that will be considered to assess the effectiveness of the intervention are the symptoms presented by the patients and the degree of overload experienced by the caregivers. The secondary outcomes considered, for patients and caregivers, are health-related quality of life, satisfaction with the intervention and the economic valuation. The outcome measures will be obtained from questionnaires completed at the start of the study (t0), at 1 week after randomisation (t1) and at 1 month after the start (t2).

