### Secondary outcome measures. Variables and measurement instruments for caregivers

Sociodemographic data for caregivers: age, sex, marital status, level of education, working outside home (yes/no), time spent providing daily care, help received in providing care, total time spent providing care, and relationship with the person receiving care.The quality of life of the caregiver will be assessed by the Family Quality of Life (FQOL) scale [51], which measures the quality of life of a family member caring for a patient with cancer. The possible scores on this scale range from 0 = worse result to 10 = best result, and the total score possible ranges from 0 to 100. Some of the items are awarded an inverse score, and so when the results are tallied and coded, the scores for those elements must be reversed. The FQOL, which has been validated for use with a Spanish-speaking population [52], addresses physical, psychological, spiritual and social aspects of the caregiver’s experience.QALY.Use made of health resources: similar to the assessment made in this respect of the patient receiving palliative care.Consumption of medication: similar to the assessment made in this respect of the patient receiving palliative care.Willingness to pay: similar to the assessment made in this respect of the patient receiving palliative care.Satisfaction, CSQ-8.

An overview of the primary and secondary outcome measures is shown in Table 1.

**Table 1 Tab1:** Measurement overview

Patient		T0	T1 7 days	T2 30 days
Primary outcome	Edmonton Symptom Assessment System (ESAS)	X	X	
Secondary outcomes	The Quality of Life of Cancer Patients (EORTC. QLQ-30)	X	X	
	Quality-Adjusted Life Year (QALY)	X	X	
	EuroQol-5D-5 L	X	X	
	Variables cost-utility analysis			
	Health Resources Consumption	X	X	X
	Medication consumption (analgesics, anxiolytics, sleeping pills)	X	X	X
	Availability to pay		X	
	Client Satisfaction Questionnaire (CSQ-8)		X	
	Other variables			
	Sociodemographic data: age, sex, marital status and level of education.	X		
	Palliative care time	X		
	Type of cancer	X		
**Caregiver**		**T0**	**T1 7 days**	**T2 30 days**
Primary outcome	Caregiver Strain Index (CSI),	X	X	
Secondary outcomes	The Quality of Life Family Version (QOL)	X	X	
	Quality-Adjusted Life Year (QALY)	X	X	
	EuroQol-5D-5 L	X	X	
	Variables cost-utility analysis			
	Health Resources Consumption	X	X	X
	Medication consumption (analgesics, anxiolytics, sleeping pills)	X	X	X
	Availability to pay		X	

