### Statistical analysis

A descriptive study will be made of the variables collected, calculating the mean and standard deviation in each case for the normally-distributed continuous variables, the confidence interval as appropriate for specific estimates, the median and interquartile range for non-normally-distributed continuous variables, and frequencies and percentages for categorical variables. The normality of the distribution will be determined by the Shapiro-Wilk test. Baseline values for the two groups will be compared.

The before and after-intervention values, in the control and intervention groups, will be compared by Student’s t-test for related samples in the case of normal continuous variables, and by the Wilcoxon T-test for paired data in the case of non-normal continuous variables.

In addition to this bivariate analysis, a multiple linear regression will be performed, in which the following dependent variables will be addressed, depending on the case: pain, fatigue, nausea, depression, anxiety, drowsiness, dyspnoea, anorexia, sleep disorders, malaise/well-being and quality of life. The independent variables considered will include both the intervention itself and also the participants’ sociodemographic variables (sex, age, level of education, marital status) and clinical variables (pathology, total time receiving palliative care). A similar procedure will be followed to determine the significance of the consumption of analgesics and the number of visits made by the nurse. All results obtained will be presented at a confidence interval of 95%. Thus, *p* < 0.05 is assumed to be statistically significant. The statistical software SPSS 23 and Epidat 4.2 will be used in this analysis.

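### The only regression that compares the groups names six covariates but not the T0 value of the outcome, which is already collected; precision is lost and chance baseline imbalance goes uncorrected

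*Protocol article*

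**What the plan says.** The Statistical analysis section describes three uses of the outcome data.

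- A baseline comparison: "Baseline values for the two groups will be compared".
- Before-after comparisons in the control and intervention groups, by a "t-test for related samples in the case of normal continuous variables" or by the Wilcoxon paired test otherwise.
- A multiple linear regression with the dependent variables "pain, fatigue, nausea, depression, anxiety, drowsiness, dyspnoea, anorexia, sleep disorders, malaise/well-being and quality of life". Its independent variables include the intervention and "sociodemographic variables (sex, age, level of education, marital status) and clinical variables (pathology, total time receiving palliative care".

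The section does not say whether the dependent variable is the T1 score or the change from T0.

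The baseline scores exist. Outcome assessment describes "questionnaires completed at the start of the study (t0), at 1 week after randomisation (t1) and at 1 month after the start (t2" as the time points. Table 1 marks T0 and T1 for the "Edmonton Symptom Assessment System (ESAS" scale, the QLQ-C30 and the EuroQol in patients, and for the CSI, the family quality-of-life scale and the EuroQol in caregivers. The Randomisation section places the first assessment "1 day before the participant receives the music delivery system from the researcher", so before any exposure.

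**The concern.** The baseline comparison describes the groups, and the paired tests look at change within a series of related measurements. Neither adjusts the treatment contrast. Of the analyses described, only the regression has the intervention as a term, so the between-group estimate rests on it.

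That model spends its named covariates on demographic and disease variables and leaves out the earlier measurement of the same quantity. Two things follow. Variation between people that T0 would explain stays in the residual and widens the confidence interval. And if the arms happen to differ in symptom level at T0, part of that difference carries into the estimated effect. Allocation is by one set of shuffled envelopes, with no stratification on symptom level described and 40 per arm planned, so a visible chance difference is realistic.

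**Working it through.** **Inputs from the protocol article (Sample size).** Relevant difference 2 points on anxiety ("Assuming a 2-point decrease in before-after anxiety to be clinically relevant"), SD 2.5, alpha 0.05, beta 0.10, 1:1 ratio, 33 per arm, raised by 20% to 40.

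**Assumed.** The T0-T1 correlation r is not given; I use 0.3, 0.5 and 0.7. I take equal SDs at T0 and T1, and read r as the correlation left once the listed covariates are fitted.

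**Step 1: the plan's own figure.** Two-sided normal approximation: n = 2 × (1.960 + 1.282)² × 2.5² / 2² = 32.8, so 33 per arm. 33 × 1.2 = 39.6, so 40. Both stated figures reproduce. With the two-sample t-test, power at 33 per arm and 2/2.5 = 0.8 SD is 0.893.

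**Step 2: residual variances.** With single-score variance s²:

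- T1 score without T0: s²
- Change from T0: 2(1 − r)s²
- T1 score with T0 as covariate: (1 − r²)s²

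The ratio of the third to the first is 1 − r². The ratio of the third to the second is (1 − r²) / [2(1 − r)] = (1 + r)/2, a saving of (1 − r)/2.

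**Step 3: power at 33 per arm.** Adjusted power uses the standardised effect 0.8 / √(variance ratio). The left block takes 2.5 as the SD of a single score and compares with a T1-score model. The right block takes 2.5 as the SD of the change and compares with a change-score model.

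| r | Ratio vs T1 score | Saving | Power | Ratio vs change | Saving | Power |
|---|---|---|---|---|---|---|
| none (T0 not added) | 1 | 0 | 0.893 | 1 | 0 | 0.893 |
| 0.3 | 0.91 | 9% | 0.918 | 0.65 | 35% | 0.978 |
| 0.5 | 0.75 | 25% | 0.959 | 0.75 | 25% | 0.959 |
| 0.7 | 0.51 | 49% | 0.994 | 0.85 | 15% | 0.935 |

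The gain grows with r in the first case and shrinks with r in the second. It is positive throughout.

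**Step 4: precision in points.** With 2.5 as a single-score SD, the standard error of the group difference at 33 per arm is 2.5 × √(2/33) = 0.615. With T0 in the model it is 0.615 × √(1 − r²) = 0.587, 0.533 or 0.440.

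**Step 5: chance imbalance.** The standard error of the baseline difference between arms is also 0.615. Given an imbalance of that size, a T1-score estimate is shifted by r × 0.615 = 0.18, 0.31 or 0.43 points. A change-score estimate is shifted in the opposite direction by (1 − r) × 0.615 = 0.43, 0.31 or 0.18 points. The target difference is 2 points.

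**The case against.** **The list is open.** The text says what the independent variables will include, and the article condenses a longer protocol. That is fair, and a fuller document may add T0. But the article goes as far as naming six covariates, and T0 is nowhere given that role, so the stated choice can be reviewed.

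**The outcome may be a change score.** The sample-size paragraph reasons in before-after terms, so T0 may already be partly used. This stands as a limit on size: the saving would be 15% to 35%, and higher correlation would reduce it. It does not remove the point, because adjustment for T0 is more precise than the change score at every r below 1.

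**The planned power is already adequate.** At 0.8 SD it is about 0.89 without T0, so the gain is modest on the protocol's own terms. A reader might infer that the trial is underpowered without T0. The documents do not support that: the stated 33 per arm reproduces, and larger gains appear only for a smaller effect that the protocol does not plan for.

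**Randomisation protects validity.** A reader might infer that the effect estimate is biased. It is not: over repeated randomisations the unadjusted estimate is unbiased, and its confidence interval already allows for chance imbalance. What remains is lost efficiency and conditional bias given the imbalance that happens to occur.

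**T0 may follow the opening of the envelope.** The text fixes T0 relative to delivery of the device, not to allocation. It still precedes exposure and is taken by nurses described as blinded, which makes it usable as a covariate.

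**Further changes might seem to follow**, such as dropping the sociodemographic covariates or adding centre. Adjusting for prespecified prognostic variables is legitimate, and nothing here depends on removing them. Nor does the article describe a CSI or EuroQol regression in which T0 could be said to be missing.

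**Conclusion.** The point holds as a matter of efficiency and conditional balance, and the plan should be amended. The T0 value of each outcome is collected and should be in the model that compares the groups. This is true whether the dependent variable is the T1 score or the change.

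The size rests on an assumed r of 0.3 to 0.7 and on what the SD of 2.5 refers to, which the protocol leaves unclear. Within that range residual variance falls by between 9% and 49%, and power at the planned effect rises from about 0.89 to somewhere between 0.92 and 0.99. The sample size is not made wrong, and no claim of systematic bias is warranted.

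**What to change.** In the Statistical analysis section, for each regression on an ESAS symptom or on quality of life, state that the dependent variable is the T1 score and add the T0 value of the same outcome to the independent variables, alongside those already listed. If the caregiver primary outcome (CSI) is modelled, use the same form: CSI at T1 as dependent variable, with CSI at T0 as a covariate.

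The cost is a sentence or two of wording and one degree of freedom per model. The T0 data are already scheduled in Table 1, and the sample size stays as it is. The change should be fixed before any comparison of outcomes by group is seen.

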### Economic evaluation

The economic evaluation performed will be a cost-utility analysis, following previous recommendations in this respect for the analysis of healthcare technologies [53]. For each group, the cost, the incremental cost, the QALY effectiveness, the incremental effectiveness and the dominance will be calculated. If there is no dominance, the final results will be expressed in terms of the incremental cost-utility ratio.

Both direct health resources costs and direct intervention-related costs will be considered. The former will be determined according to the public prices reported by the Andalusian Public Health System [54]. The cost of the direct resources incurred in the intervention will be estimated according to the corresponding retail prices. The EuroQol-5D-5 L questionnaire will be used to calculate the QALY variable. The variables subject to uncertainty will be subjected to univariate and multivariate sensitivity analyses.

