## Discussion

We present the protocol for a double-blind multicentre randomised controlled trial of the effects of music therapy. The main aim of this project is to employ cost-utility analysis to evaluate the effectiveness and cost-effectiveness of a musical therapy intervention (as a complementary therapy) for cancer patients and their caregivers in at-home palliative care, compared with usual treatment.

The principal strength (and novel aspect) of this study resides in the fact that in the intervention, each participant chooses the music they believe will enhance their well-being. This contrasts with most other studies in this field, where the music is predetermined or grouped into broad categories.

Another novel aspect in the study design is the use of the double-blind system to reduce bias and maximise the reliability of the results obtained. In addition, we aim to provide new evidence on the cost-effectiveness of this kind of intervention (to our knowledge, virtually no evidence has previously been reported in this regard).

The study proposed will improve our understanding of how music therapy impacts on the physical and psychological situations of patients and their caregivers.

Potential benefits of musical therapy include the decreased consumption of medication for problems such as anxiety, pain and sleeplessness, the alleviation of symptoms, improved mood, reduced caregiver strain, enhanced health-related quality of life and greater patient and caregiver satisfaction.

As the intervention has no side effects, it can be applied in conjunction with usual short-term clinical practice, if its effectiveness is demonstrated. This type of complementary therapy could benefit the sustainable implementation and maintenance of the at-home palliative care provided to cancer patients, and at the same time improve the quality of life of their caregivers.

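### The cost-utility analysis describes incremental QALYs with no adjustment for the T0 EQ-5D-5L utility that the trial already collects, at an avoidable cost in precision

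*Protocol article*

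**What the plan says.** The Economic evaluation section of the protocol article sets out a sequence: "For each group, the cost, the incremental cost, the QALY effectiveness, the incremental effectiveness and the dominance will be calculated". It continues: "If there is no dominance, the final results will be expressed in terms of the incremental cost-utility ratio". The utility source is fixed by "The EuroQol-5D-5 L questionnaire will be used to calculate the QALY variable". The section does not say how utilities become QALYs, over what horizon, or whether the group comparison is adjusted.

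The Statistical analysis section does specify a regression. Its outcomes are the individual symptoms and quality of life, with a similar procedure for analgesic use and nurse visits. Its predictors are the intervention plus sociodemographic and clinical variables. QALYs are not named among the outcomes, and no T0 outcome value is among the predictors.

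Table 1 schedules the EQ-5D-5L and the QALY at T0 and T1 (7 days) only, for patients and for caregivers. It schedules resource and medication use at T0, T1 and T2 (30 days). The Outcome assessment section describes a start-of-study questionnaire and then further ones "at 1 week after randomisation (t1) and at 1 month after the start (t2", with no exception for the EQ-5D-5L. The Randomisation section likewise has the nurses evaluating the study variables at three time points.

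The Discussion gives the economic question high standing: "The main aim of this project is to employ cost-utility analysis to evaluate the effectiveness and cost-effectiveness of a musical therapy intervention".

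**The concern.** T0 utility matters more for a QALY than a baseline covariate usually does. If a QALY is an area under the utility curve that starts at T0, the T0 utility is an arithmetic component of the outcome. A chance difference between the arms before treatment then passes directly into the increment. If the QALY gain is instead a change from T0, the T0 gap enters with the opposite sign.

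The protocol reports a cost-utility ratio only when neither option dominates, so the sign of the QALY increment decides how the result is reported. At the planned sample sizes, a chance T0 gap can be as large as a modest treatment effect. The covariate that would remove most of this noise is already scheduled, yet the described comparison does not use it.

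**Working it through.** **Inputs from the protocol article.** Patients: 33 per arm, raised to 40. Caregivers: 34 per arm, raised to 41. EQ-5D-5L at T0 and T1 in Table 1. Resource data to day 30.

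**The plan's own figure.** A 2-point difference, SD 2.5, alpha 0.05 (taken as two-sided) and power 0.90 give 33 per arm by the normal approximation (34 by the exact t calculation), and 33 × 1.2 = 39.6, so 40. The patient number reproduces. It was set for anxiety. The article gives no figure for QALYs, utility SD or T0–T1 correlation.

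**Assumptions.** Equal utility SD at T0 and T1, set to 1. Correlation rho = 0.5, range 0.3 to 0.7. A treatment effect d on T1 utility, in SD units.

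**General form.** Write the QALY, up to a time constant, as a·u0 + b·u1.
- Unadjusted variance: a² + b² + 2ab·rho
- Variance given u0: b²(1 − rho²)
- Effect: b·d
- SE of a group difference: √(variance × 2/n)

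**Three constructions that the text allows.**
1. T0–T1 trapezoid over 7 days: a = b = 0.5. T0 weight 50%.
2. 30-day horizon with T1 carried forward: a = 3.5/30 = 0.117, b = 0.883. T0 weight about 12%. A trapezoid through a measured T2 gives T0 the same direct weight.
3. Change from T0: a = −1, b = 1.

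**Variances at rho 0.5.**
- Construction 1: (1 + 0.5)/2 = 0.75 unadjusted; 0.25 × 0.75 = 0.1875 adjusted. Cut 75%.
- Construction 2: 0.0136 + 0.7803 + 0.1031 = 0.897 unadjusted; 0.7803 × 0.75 = 0.585 adjusted. Cut 35%.
- Construction 3: 2(1 − 0.5) = 1.00 unadjusted; 0.75 adjusted. Cut 25%.

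| Construction | Cut, rho 0.3 | Cut, rho 0.5 | Cut, rho 0.7 |
|---|---|---|---|
| 7-day trapezoid | 65% | 75% | 85% |
| 30 days, T1 carried forward | 17% | 35% | 58% |
| Change from T0 | 35% | 25% | 15% |

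**Chance of a wrong-signed increment.** Take d = 0.2, n = 33 and rho = 0.5, so √(2/33) = 0.246.
- 7-day trapezoid: 0.1/(√0.75 × 0.246) = 0.469, giving 32%.
- 30 days: 0.1767/(√0.897 × 0.246) = 0.758, giving 22%.
- Change from T0: 0.2/(1 × 0.246) = 0.812, giving 21%.
- Adjusted, all three: 0.2/(√0.75 × 0.246) = 0.938, giving 17%. The constant b cancels, so after adjustment the construction no longer matters.

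**Power, as a secondary illustration.** For d = 0.5, n = 33 and rho = 0.5 (two-sided 0.05, noncentral t), power rises from 21%, 46% and 52% respectively to 64%.

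**On the utility scale.** With an assumed utility SD of 0.15 to 0.30 and 40 per arm, the SE of the chance T0 gap is SD × √(2/40) = 0.034 to 0.067. Under the 7-day trapezoid, half of the 95% range of that gap is ±0.033 to ±0.066 in utility. Multiplied by 7/365, this is ±0.0006 to ±0.0013 QALY.

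**The case against.** The strongest reply is that the article never calls the increment raw or unadjusted. It lists outputs and cites recommendations that are not available here, and a condensed article may leave the estimator to a fuller plan. This stands against a stronger reading that a reader might infer, namely that the protocol commits to a crude difference in which half of any T0 gap is counted as benefit. The documents do not support that. The one-half weight needs a two-point trapezoid ending at T1, which is not stated. Over 30 days the weight is about 12%, and the text outside Table 1 implies a T2 assessment.

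Two further points also stand. Under randomisation a T0 gap is chance, so the loss is one of precision and not bias. And the economic section names no significance test on QALYs, so the power figures are only illustrative; the wrong-sign probability is closer to how the result will be used.

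The reply does not dispose of the point. The section does give a sequence (group QALYs, increment, dominance) with no model, while the article spells out covariates where it intends adjustment. The planned sensitivity analyses address uncertain variables and do not set the base-case estimator. Adjustment helped under each of the three constructions at every correlation tried.

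**Conclusion.** The point holds as a recommended improvement to the described analysis. The comparison of group QALYs carries no T0 utility adjustment, and the trial will hold the covariate needed to make one. At rho 0.5 the avoidable share of the variance runs from 25% to 75% depending on the QALY construction; across rho 0.3 to 0.7 it runs from 15% to 85%. The reduction in wrong-sign risk is large for a 7-day trapezoid (32% to 17%) and modest for the other two constructions (22% or 21% to 17%), given a true T1 effect of 0.2 SD and 33 per arm.

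These figures rest on an assumed correlation, equal SDs at the two visits and an assumed effect, none of which the article supplies. The weight on T0 cannot be settled until the EQ-5D-5L schedule is made consistent: T0 and T1 in Table 1, three time points in Outcome assessment and Randomisation, and costs running to day 30.

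**What to change.** Add to Economic evaluation: *Incremental QALYs, for patients and for caregivers separately, will be the group coefficient from a regression of each participant's QALY on study group and T0 EQ-5D-5L utility. This estimate will be used to judge dominance and to form the incremental cost-utility ratio. The unadjusted difference will be reported as a sensitivity analysis.*

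In the same revision, reconcile the EQ-5D-5L time points in Table 1 with Outcome assessment and Randomisation, and state the QALY horizon and construction alongside the 30-day resource data.

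The cost is a sentence or two of text and one regression per sample, on data already scheduled. Participants without a T0 EQ-5D-5L would drop out of the model, but they could not have a QALY that starts at T0 in any case. An added T2 EQ-5D-5L would be extra collection only if the sponsor resolves the schedule conflict in that direction.
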